The identification of patients who are at high risk of ACS after surgical repair of rAAA in the operating room could allow detecting and managing earlier patients with an increase in intra-abdominal pressure and ACS. Several factors related to the occurrence of intra-abdominal hypertension and ACS has been identified in the literature.^[12,16,19]^ Ruptured abdominal aneurysm is one of the risk factors. Among the others risk factors identified during the last consensus conference, we selected 6 that could be diagnosed in the pre- and intraoperative period: systolic blood pressure, body mass index, massive fluid resuscitation, massive transfusion, hypothermia, and acidosis.^[3,7]^ We selected 2 additional criteria, anemia and cardiac arrest, more specific to rAAA. These 8 criteria are easily collected during the initial management, correspond to data of the usual management in these patients and easy to access even in the operating room. We chose to analyze both surgical techniques (open or endovascular) together because the prevalence of ACS in the literature is the same.^[10,12–17,21,22]^

Previously, we have conducted a retrospective pilot study in our center, which found that with the threshold of 3 among 8 selected pre- and intraoperative criteria, we would predict an ACS occurrence with a 54% positive predictive value and a 92% negative predictive value. The prevalence of ACS in our study was 17% and the mortality rate in the group of patients with an ACS was 37.5%.^[23]^ Nevertheless, it was a retrospective, monocentric study with a small population without systematically measure of intra-abdominal pressure and with posteriori diagnosis of ACS. A multicentric prospective study was clearly needed to confirm these results.

This study aims to specify a predictive test for the occurrence of an ACS after rAAA surgery. Early detection of the ACS could enable rapid management of patients and influence the mortality rate.

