### Study design

2.1

This is a French prospective cohort study on patients presented a rAAA. The number of patients to be included is 165. All patients with a rAAA will be consecutively included, whatever the surgical treatment, open surgery or endovascular surgery. The estimated duration of recruitment is 30 months.

The primary endpoint of the study is the occurrence of an ACS within 5 days after surgery. The predictive capacity of the occurrence of ACS will be measured by sensitivity, specificity, positive and negative likelihood ratio, positive and negative predictive value.

The secondary endpoints are the occurrence of an ACS within 5 days after surgery according to the type of surgical technique (open surgery or endovascular surgery), death within 30 days of intervention, and hospital stay (intensive care unit stay and total hospital stay).

The 8 pre- and per-operative criteria are:

(1)Anemia with hemoglobin < 10 g/dL(2)Persistent of a systolic blood pressure lower than 90 mm Hg(3)Cardiac arrest(4)Body mass index (BMI) > 30(5)Massive fluid resuscitation of more than 3500 mL/h for at least one hour(6)Transfusion ≥ 10 units of red blood cells since the beginning of the treatment(7)Hypothermia with a temperature of 33°C or below(8)Acidosis with a pH ≤ 7.2.

When a patient with an rAAA arrives at the emergency room, he can be included in the protocol. According to its clinical condition, information on the study will be given to him and nonobjection consent. If the patient is unable to give consent, his or her family will be contacted to confirm non opposition to data collection. The data collected are usual and the management of rAAA is the same. No further examination is necessary for the study because it is an observational prospective study.

At admission, the following data will be collected: age, gender, weight, height, BMI, medical, and surgical history. During the pre- and intraoperative period: pre- and perioperative criteria, abdominal closure conditions, type of intervention, surgical procedure, type of anesthesia, clamping time, blood loss, and anesthetic conditions.

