### Objectives

2.2

The primary objective of the study is to assess the qualities of a predictive test on the occurrence of this syndrome after surgery of rAAA.

Secondary outcomes were to compare the test between surgical techniques (endovascular or open), 30 days mortality rate and the duration of hospitalization (intensive care unit stay and total hospital stay).

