### Statistical analysis

2.6

The quantitative variables will be described using the mean and standard deviation, the median, and the minimum and maximum values. The qualitative variables will be described by the proportion and the percentage of each class.

As previously demonstrated, the test will be considered positive if the patient presents at least 3 criteria on the 8.^[23]^ Specificity, sensitivity, positive, and negative likelihood ratios, positive and negative predictive values with their confidence interval will be calculated for the new predictive test.

The comparison between surgical techniques used will be carried out with a Chi^2^ test or an exact Fisher test. A logistic regression carried out on sensitivity analysis will be done to build a predictive score and confirm the result.

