### Sample size calculation

2.7

For a sensitivity of 0.75, a precision of 0.15 and an alpha risk of 5%, the number of subjects required is 33 patients with ACS. For a prevalence of ACS at 20%, the number of patients required is 165.^[10,12–19,21,22]^

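### The protocol sets out to compare the test between open and endovascular repair, but its only technique-specific endpoint is ACS occurrence, which cannot show whether the 3-of-8 rule works equally well in both

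*Protocol article*

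**What the plan says.** Four places in the protocol article bear on the comparison of techniques.

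- **Objectives (2.2):** "Secondary outcomes were to compare the test between surgical techniques (endovascular or open"). The thing compared is the test.
- **Study design (2.1):** "The secondary endpoints are the occurrence of an ACS within 5 days after surgery according to the type of surgical technique". The thing compared is how often ACS occurs. No other endpoint is defined by technique.
- **Statistical analysis (2.6):** "The comparison between surgical techniques used will be carried out with a Chi"-square or a Fisher exact test. The variable is not named. Just before this, the rule is fixed ("the test will be considered positive if the patient presents at least 3 criteria on the 8") and the accuracy measures are listed once: "positive and negative predictive values with their confidence interval will be calculated for the new predictive test". No split by technique is mentioned. The logistic regression that follows is meant to build a score, and technique is not named as a term in it.
- **Background (1):** "We chose to analyze both surgical techniques (open or endovascular) together because the prevalence of ACS in the literature is the same".

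**The concern.** Two different questions are treated as one. Whether ACS is equally common after open and endovascular repair is a question about incidence. Whether a count of at least 3 of 8 criteria identifies the patients who will develop ACS equally well after each is a question about sensitivity and specificity. Objectives asks the second question; the endpoint in Study design answers the first.

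The Background makes the same substitution when it gives equal prevalence as the reason for analysing the techniques together. Sensitivity is conditional on having ACS and specificity on not having it, so neither can be inferred from how common ACS is. Several of the eight criteria (fluid rate, transfusion, temperature, pH) could plausibly be met at different rates in the two operations; the document gives no data either way.

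The abstract looks ahead to using the test when considering prophylactic decompression, and the Discussion lists the harms of an open abdomen. Whether one cut-off serves both techniques therefore matters to a reader of the results, and the stated endpoint would leave it unanswered.

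**Working it through.** **1. The plan's own figure.** Sample size calculation states: "For a sensitivity of 0.75, a precision of 0.15 and an alpha risk of 5%, the number of subjects required is 33 patients with ACS". Using a two-sided 5% level:

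n = 1.96² × 0.75 × 0.25 / 0.15² = 32.01, rounded up to 33; 33 / 0.20 = 165.

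Both figures reproduce. They concern sensitivity in the whole cohort, not by technique.

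**2. Does occurrence carry information about accuracy?** The counts below are illustrative; the article gives no split by technique.

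| Assumed data | Test of ACS occurrence | Accuracy |
|---|---|---|
| ACS in 16/80 against 17/85 (20% each) | p = 1.00 | Sensitivity could be 15/16 (94%) against 10/17 (59%), Fisher p = 0.039 |
| ACS in 8/82 against 25/83 | chi-square p = 0.001 | Sensitivity and specificity could be identical |

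Equal occurrence is compatible with unequal sensitivity, and unequal occurrence with equal accuracy. The comparison is uninformative about the objective in both directions.

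**3. What could a direct comparison of sensitivity deliver?** Inputs: 33 ACS cases and sensitivity 0.75 (Sample size calculation). The open/endovascular split of those cases is assumed. The half-width for the difference is 1.96 × √[0.75 × 0.25 × (1/n₁ + 1/n₂)]:

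- 16/17: 1.96 × √(0.1875 × 0.1213) = 0.30
- 23/10: 1.96 × √(0.1875 × 0.1435) = 0.32
- 26/7: 1.96 × √(0.1875 × 0.1813) = 0.36

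Within one technique, the half-width 1.96 × √(0.1875/n) is about 0.21 in each group at 16/17. At 26/7 it is about 0.17 in the larger group and 0.32 in the smaller.

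Exact power of the two-sided Fisher test at 5% for true sensitivities of 0.85 and 0.65 (also assumed) comes from summing the binomial probabilities of all tables with p ≤ 0.05:

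| Split of the 33 ACS cases | 0.85 in the first-listed group | 0.85 in the second-listed group |
|---|---|---|
| 16/17 | 0.175 | 0.214 |
| 23/10 | 0.203 | 0.106 |
| 26/7 | 0.172 | 0.054 |

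Power is low throughout, and lowest when the smaller group has the higher sensitivity.

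**The case against.** The strongest reply is that this is a condensed journal article. Which 2×2 table is tested, and whether accuracy is tabulated by stratum, are details that the full protocol or analysis plan may supply. That stands as far as missing detail goes. It does not cover the mismatch, because the objective, the technique-specific endpoint and the reason for pooling are all printed here and do not agree.

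Several stronger readings are tempting, and the document does not support them.

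- **That the planned test compares ACS occurrence, or is the wrong test.** This may be inferred by joining Statistical analysis to Study design, but the former names no variable. Its sentence follows directly on the accuracy measures, and a Fisher test could properly compare sensitivity or specificity between techniques. The choice of test is not the defect.
- **That the comparison is confounded because technique depends on patient condition.** The article does not say how technique is chosen and makes no causal claim about it. Comparing a test's accuracy across subgroups is not an estimate of a treatment effect. An estimate adjusted for preoperative severity is not supported either: the only named severity scores, APACHE II and SOFA, are listed as postoperative data.
- **That a non-significant result will be used to justify pooling.** No section says so. Pooling is presented as a choice made in advance. The caution about p > 0.05 is advice for reporting, not a criticism of a stated plan.

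It is also fair to say that the split and the contrasting sensitivities used above are assumptions, and that low power in a secondary subgroup comparison is a separate matter that the fix does not cure.

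**Conclusion.** The point holds as an inconsistency between a secondary objective and its endpoint, with a pooling rationale that does not bear on accuracy. Followed as written, the endpoint in Study design cannot meet the aim in Objectives. That conclusion is logical and does not depend on any assumed number; the 16/80 and 17/85 example only makes it visible.

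The size of what a proper comparison could show does rest on assumptions. With 33 ACS cases, an unstated split taken between 16/17 and 26/7, and sensitivity near 0.75, a difference in sensitivity would be known to about ±0.30 to ±0.36. A true contrast of 0.85 against 0.65 would be detected with probability of roughly 5% to 21%. The comparison can describe, but it cannot establish that the rule performs equally in both techniques.

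The matter should be corrected, but it is confined to one secondary objective. The pooled primary estimate remains computable, and the sample size of 165 is correct for the precision it states.

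**What to change.** Reconcile Study design, Objectives and Statistical analysis as follows.

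1. Report sensitivity, specificity, predictive values and likelihood ratios separately for open and endovascular repair, with confidence intervals (exact ones for the proportions).
2. Name the variable compared: test positivity by technique within ACS patients (sensitivity) and, separately, within non-ACS patients (specificity). Use Fisher's test and give the difference with its confidence interval.
3. Label this comparison exploratory, and state that p > 0.05 will not be read as equivalence.
4. Keep ACS occurrence by technique as a separate, descriptive endpoint.
5. In the Background, drop equal prevalence as the reason for pooling accuracy.

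The data needed (type of operation, the eight criteria and adjudicated ACS status) are already collected, so only wording changes. The price is wide stratum-specific intervals, which should be presented as such.

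### A score fitted to the same 165 patients cannot independently confirm the fixed rule of at least 3 of 8 criteria, and with 28 to 33 events its apparent performance is likely to be optimistic

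*Protocol article*

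**What the plan says.** Section 2.6 (Statistical analysis) of the protocol article fixes the test in advance from the pilot: a patient is test-positive with three or more of the eight criteria listed in section 2.1. Sensitivity, specificity, likelihood ratios and predictive values with confidence intervals are the main results. The section then adds: "A logistic regression carried out on sensitivity analysis will be done to build a predictive score and confirm the result".

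Section 2.7 gives the sample size. It starts from "For a sensitivity of 0.75, a precision of 0.15 and an alpha risk of 5"%, concludes that "the number of subjects required is 33 patients with ACS", and continues: "For a prevalence of ACS at 20%, the number of patients required is 165". The Background reports a lower pilot figure: "The prevalence of ACS in our study was 17"%.

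The article describes one cohort and no separate validation sample. It does not say how many terms enter the regression or how the model is fitted.

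**The concern.** The sentence gives one regression two jobs: to derive a new score, and to confirm the result. Both use the same patients. Weights chosen to fit these 165 patients will reproduce whatever pattern the patients happen to show, so agreement between the score and the fixed rule is not a second piece of evidence.

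The number of events adds to this. The sample size was set to estimate one proportion, and the expected number of ACS cases is small for estimating eight weights. A score judged in the data that produced it tends to look better than it will in new patients, and its predicted risks tend to be too extreme. The study exists because the pilot was small and retrospective and needed confirmation. A refitted score that appears to outperform the fixed rule could draw attention from the one result this cohort can properly confirm.

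**Working it through.** **1. The plan's own figure.** Inputs from section 2.7: sensitivity p = 0.75, precision d = 0.15 (taken as the half-width of the interval), alpha 5% (taken as two-sided, z = 1.96).

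n = z² × p(1 − p) / d² = 3.84 × 0.1875 / 0.0225 = 32.01, rounded up to 33 events. Then 33 / 0.20 = 165 patients. Both figures are reproduced. Nothing in the calculation concerns a regression model.

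**2. Events per coefficient, if the eight criteria are the candidates.**

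- At 17% prevalence: 165 × 0.17 = 28.05 events; 28.05 / 8 = 3.5.
- At 20% prevalence: 165 × 0.20 = 33 events; 33 / 8 = 4.1.
- Allowing for chance, the 95% binomial ranges are 19 to 38 events at 17% and 23 to 43 at 20%, or about 2.4 to 5.4 per coefficient overall.

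**3. Size needed for limited shrinkage.** With P = 8 coefficients and target shrinkage S = 0.9, N = P / [(S − 1) × ln(1 − R²/S)]. Here R² is the Cox-Snell value, equal to the assumed Nagelkerke R² times its maximum (0.598 at 17% prevalence, 0.632 at 20%). Example at 20% with Nagelkerke 0.30: R² = 0.30 × 0.632 = 0.190, and N = 8 / [−0.1 × ln(1 − 0.190/0.9)], which is about 338. The Nagelkerke values are assumptions; the documents give none.

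| Assumed Nagelkerke R² | Patients needed | Events needed | Expected shrinkage at N = 165 |
|---|---|---|---|
| 0.15 | 719 to 762 | 130 to 144 | 0.67 to 0.68 |
| 0.30 | 338 to 360 | 62 to 68 | 0.81 to 0.82 |
| 0.50 | 185 to 199 | 34 to 37 | 0.88 to 0.89 |

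**4. Simulation.** An unpenalised eight-term logistic model was fitted to 165 patients and tested on 20,000 new ones, with 300 runs per scenario. Assumptions: independent criteria with frequencies of 8% to 40% and the same odds ratio for each. Optimism is apparent c minus c in new patients, taken before rounding.

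| ACS prevalence | Odds ratio per criterion | Apparent c | c in new patients | Optimism | Median calibration slope |
|---|---|---|---|---|---|
| 17% | 1.65 | 0.717 | 0.599 | 0.118 | 0.44 |
| 17% | 2.72 | 0.812 | 0.738 | 0.075 | 0.67 |
| 17% | 4.48 | 0.879 | 0.833 | 0.046 | 0.76 |
| 20% | 1.65 | 0.703 | 0.598 | 0.105 | 0.43 |
| 20% | 2.72 | 0.805 | 0.738 | 0.067 | 0.70 |
| 20% | 4.48 | 0.868 | 0.831 | 0.037 | 0.79 |

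With no true association, apparent c still averaged 0.65 to 0.66, against 0.50 in new patients.

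A separate simulation with correlated criteria and 20% prevalence (500 datasets per scenario) agrees in direction. At an odds ratio of 1.65, apparent c was 0.75 against 0.67 in new patients, slope 0.57. At 2.2, it was 0.83 against 0.79, slope 0.75.

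**The case against.** The strongest reply is that the regression is secondary. The primary objective rests on a rule fixed before this cohort and not fitted in it, and the sample size serves that rule. A reader might infer that overfitting undermines the trial's main result, or that the cohort can confirm nothing. The documents do not support either: the estimates for the fixed rule do not depend on the regression, and the regression can still explore whether the criteria, or their count, are associated with ACS.

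The second reply is that an unpenalised eight-term model is nowhere stated. This stands. If the criterion count entered as a single term, there would be 28 to 33 events per coefficient. However, the eight criteria are the only candidate predictors the article puts forward for study, and choosing a few of them from the data would still draw on all eight. Penalisation and internal validation may be set out in a full protocol or SAP, so their absence from the article is not held against it.

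Third, the magnitudes rest on assumed frequencies and effects. This also stands, and three further inferences should not be drawn:

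- The documents do not show that some criteria are rare.
- A reader might conclude from such simulations that a weighted score is no better than the count. Equal odds ratios make the count the correct model by design, so this is not a finding.
- The Discussion's future randomised study compares early with delayed laparostomy. The article does not say that a regression score would select its patients.

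None of these replies rescues the stated purpose. Whatever the fitting method, a score built in these patients is not independent confirmation of the rule tested in them.

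**Conclusion.** The concern holds in a limited form. The confirmatory role given to the regression in section 2.6 is wrong as written, and no detail in an unseen SAP could make a score derived in this cohort an independent check. The overfitting is conditional: with eight candidate terms, no penalisation and 28 to 33 expected events, apparent c would be too high by roughly 0.04 to 0.12 when the criteria carry signal, with calibration slopes of about 0.4 to 0.8. The direction was the same in every scenario run; the size depends on the unknown strength of the signal. The matter should be fixed, but it concerns a secondary analysis.

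**What to change.** In section 2.6:

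- Delete the closing clause that gives the regression a confirming role, and state that the fixed rule of at least 3 of 8 is the only confirmatory test.
- Label the regression score exploratory.
- Fit it with penalisation (ridge or Firth) on the eight prespecified criteria, without data-driven selection.
- Report the c-statistic and calibration slope corrected for optimism by bootstrap.
- Compare the score with the unweighted 0 to 8 count.

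The cost is a few lines of text and modest extra analysis, with no additional patients. The drawback for the sponsor is that the reported performance of the score will look less favourable.

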### Sample size calculation

2.7

For a sensitivity of 0.75, a precision of 0.15 and an alpha risk of 5%, the number of subjects required is 33 patients with ACS. For a prevalence of ACS at 20%, the number of patients required is 165.^[10,12–19,21,22]^

## Discussion

3

The estimated recruitment is 30 months and the number of patients to be included is 165. The recruitment will be consecutive and with no patient selection profile. All patients with a rAAA will be consecutively included in each center.

Inclusion will initially begin in our region and then extend to nonregional centers. This progressive opening of the centers will ensure the correct inclusion of patients. The principal investigator will visit each center to explain the criteria measurement procedures and the intra bladder pressure measurement to ensure homogenous management.

Decompressive laparotomy is the only treatment for ACS and there is no recommendation about the prophylactic management of the ACS. In the literature, we found that early decompressive laparotomy appears to improve survival than late decompression.^[7]^

A prophylactic decompression could be proposed to avoid ACS after rAAA surgery, and prevent occurrence of complications. But, there are complications after an open abdomen, especially for a long time, such as cutaneous complications, enterocutaneous fistula, intra-abdominal infection or evisceration, so it would necessary to early detect the ACS and identify patients at risk to develop an ACS, and do not propose systematic laparostomy at the end of surgery.

Later, the aim of the future study will be to screen ACS and manage patient as soon as possible to avoid it. We would like to carry out a prospective randomized study between early laparostomy versus delayed laparostomy to compare 30 days mortality rate.
